## Abstract

**Background:**

Osteoarthritis (OA) of the hip is a major cause of functional disability and reduced quality of life. Management options aim to reduce pain and improve or maintain physical functioning. Current evidence indicates that therapeutic exercise has a beneficial but short-term effect on pain and disability, with poor long-term benefit. The optimal content, duration and type of exercise are yet to be ascertained. There has been little scientific investigation into the effectiveness of manual therapy in hip OA. Only one randomized controlled trial (RCT) found greater improvements in patient-perceived improvement and physical function with manual therapy, compared to exercise therapy.

**Methods and design:**

An assessor-blind multicentre RCT will be undertaken to compare the effect of a combination of manual therapy and exercise therapy, exercise therapy only, and a waiting-list control on physical function in hip OA. One hundred and fifty people with a diagnosis of hip OA will be recruited and randomly allocated to one of 3 groups: exercise therapy, exercise therapy with manual therapy and a waiting-list control. Subjects in the intervention groups will attend physiotherapy for 6–8 sessions over 8 weeks. Those in the control group will remain on the waiting list until after this time and will then be re-randomised to one of the two intervention groups. Outcome measures will include physical function (WOMAC), pain severity (numerical rating scale), patient perceived change (7-point Likert scale), quality of life (SF-36), mood (hospital anxiety and depression scale), patient satisfaction, physical activity (IPAQ) and physical measures of range of motion, 50-foot walk and repeated sit-to stand tests.

**Discussion:**

This RCT will compare the effectiveness of the addition of manual therapy to exercise therapy to exercise therapy only and a waiting-list control in hip OA. A high quality methodology will be used in keeping with CONSORT guidelines. The results will contribute to the evidence base regarding the clinical efficacy for physiotherapy interventions in hip OA.

**Trial Registration:**

Number: NCT00709566

## Background

Osteoarthritis can be defined as a group of overlapping distinct diseases, which may have different aetiologies but with similar biologic, morphologic and clinical outcomes. The articular cartilage degenerates with the development of fibrillation and fissures, and full thickness loss of the joint surface' [1]. It is estimated that by 2030 the proportion of people with OA will have risen from 20% to 30% in those aged 60 years or over [2]. Increasing life expectancy, decreasing physical activity, and increasing body weight are all considered as underlying factors. OA is the most common form of arthritis and is associated with a considerable cost to the individual and to society. A World Health Organisation report identified OA as the 8^th ^leading cause of non-fatal burden in the world in 2000, accounting for 2.6% of total years lost due to disability [3]. It is commonly associated with other medical conditions such as cardiovascular disease, respiratory disease and diabetes [4,5]. Prevalence of hip OA varies between 1.4% and 3.5% based on radiographic definitions [6], and between 0.7 and 4.4% for symptomatic hip OA [7]. Physical function and physical activity levels are reduced in hip OA and consequently this can impact on quality of life [8-10] and has associated psychosocial impact such as depression [11-13].

To date, there is no cure for OA, so the principles of management are to control pain, improve function and reduce disability [14,15]. Contemporary thinking is that non-pharmacological measures such as patient education, weight loss, physiotherapy, occupational therapy, and exercise should be tried first, with pharmacological intervention used as an adjunct [16]. Physiotherapy is the most common non-pharmacological intervention prescribed for OA [17] and aims to reduce pain and restore or maintain optimum physical functioning [18].

Physiotherapy can comprise a number of different interventions, including electrotherapy, massage and the provision of orthotics, but a questionnaire survey of Irish physiotherapists in public and private settings identified that the most common interventions used by physiotherapists to manage hip OA were exercise therapy (100%), education (99%) and manual therapy (96%) [19].

### Evidence for Exercise Therapy

Therapeutic exercise has been recommended as a key component of the management of hip OA in a number of clinical guidelines [20-24]. It can comprise joint-specific exercise for range of motion, strengthening of muscles around the hip and general aerobic conditioning. It can take place on land or in water (hydrotherapy) and can be done in a supervised setting or as a home-based self-directed programme [25]. A number of studies have evaluated the effect of exercise therapy in hip OA. Different forms of exercise therapy have been investigated such as hydrotherapy [26-30] and strengthening [29,31-34]. Exercise has also been used as a control intervention with the provision of advice/education and a programme of home exercises [28,35].

Although a number of systematic reviews have been undertaken evaluating the effectiveness of exercise therapy in OA, most of these have included knee and hip OA studies [36-39], with just one focussing specifically on hip OA [40]. This review, based on nine RCTs, found that therapeutic exercise, with a strengthening component, was an efficacious treatment for pain in hip OA. To date, the benefits of exercise for improving pain and function in hip OA appear to be short-term only [32,34,38] However, many of the studies undertaken have combined hip and knee OA patients [29,30,32,41] thereby limiting the value of the results. These studies were not powered sufficiently to observe the effect of exercise on hip OA only. Secondly, the same exercise regime was used by patients with hip and knee OA, thus the specificity of the exercise regime to hip OA is questionable. Certain flaws existed in many of the studies such as inadequate sample size [29,34], lack of intention-to-treat analysis [41,42] and lack of blinding of outcome assessors [29,42]. Due to the nature of exercise based interventions, blinding of the subjects and treating therapists was not possible in any of the studies [43].

### Evidence for Manual Therapy

Manual therapy is a commonly used intervention in the management of musculoskeletal dysfunction in physiotherapy. It can be defined as 'a clinical approach involving specific hands-on techniques including, but not limited to specific hands-on mobilization, that are used by the physical therapist to diagnose and treat soft tissues and joint structures for the purpose of modulating pain; increasing range of motion; reducing or eliminating soft tissue inflammation; inducing relaxation; improving repair, extensibility or stability of contractile or non-contractile tissue; facilitating movement and improving function' [44] (pg 180). Manual therapy comprises manipulation and mobilisation techniques. Manipulation consists of forceful, high velocity thrusts, whilst mobilisations are less vigorous techniques which are used more often than manipulation for peripheral joint pain and stiffness [17]. Despite its widespread use clinically, there is little scientific evidence to substantiate the effectiveness of manual therapy in reducing pain or improving function in OA [45]. Specifically in hip OA, there has been considerably less research into the effectiveness of manual therapy compared with exercise therapy.

To these authors' knowledge, only one clinical trial has been conducted evaluating manual therapy in hip OA [33]. Manual therapy, which encompassed manipulation techniques and stretching, was compared head to head against exercise therapy. Results at 5 weeks demonstrated 81% improvement in the manual therapy group and 50% in the exercise therapy group. This was based on a 6-point Likert scale of patient perceived general improvement. These data may not be relevant to clinical practice in Ireland for two reasons. Firstly, in Ireland, therapists more commonly use mobilization techniques developed by Mulligan [46] and Maitland [47] rather than manipulation [19]. Secondly, current clinical practice shows that manual therapy is frequently used in combination with other interventions such as exercise therapy [19] and there is a need to conduct randomized controlled trials that are transferable to clinical practice [48]. To date, no known studies have evaluated the combined effect of manual therapy and exercise in hip OA. Recently published UK clinical guidelines on the care and management of osteoarthritis in adults recommended manual therapy as an adjunctive treatment to core treatments of exercise and education in OA, particularly hip OA [20].

### Predictors of response to treatment

Treatment effectiveness can be improved by matching treatment to patient characteristics to determine what works best for whom. Few studies have evaluated predictors of response to physiotherapy in hip OA. Hoeksma et al [49] found that patients with mild/moderate radiographic changes who received manual therapy had significantly better range of motion outcomes than those with severe changes. Manual therapy had no differential effect on subgroups of patients defined by baseline pain or hip function. This secondary analysis did not evaluate the outcome of the exercise intervention on different subgroups. Female gender, low co-morbidity, absence of depressive symptoms and a history of receiving complementary medicine in the previous 12 months were the most stable predictors of outcome in a non-randomised study of inpatient rehabilitation for hip or knee OA [50]. In this proposed study, patients of varying severity will be included and it is possible that treatment effects may be different in groups of patients with different characteristics, such as x-ray severity and symptomatic severity.

In summary, a multi-centre randomised controlled trial that compares the clinical effectiveness of a combination of manual therapy and exercise therapy, exercise therapy only and a waiting-list control will be conducted. This study also will examine if any clinical baseline features predict response to treatment as a secondary analysis.

## Methods

### Aim

The primary aim of this study is to compare the effect of a combination of manual therapy and exercise therapy, exercise therapy only and a waiting-list control on physical function in hip OA.

A secondary aim of the study will be to investigate the effect of baseline variables such as age, gender, body mass index, disease severity, baseline pain, physical function, mood and co-morbidities on treatment outcome.

### Study Design

A multi-centre assessor blind RCT that evaluates the clinical effectiveness of two physiotherapy interventions for patients with osteoarthritis of the hip will be conducted. The methodology will follow CONSORT (Consolidation of Standards of Reporting Trials) guidelines [51,52].

### Ethics

Ethical approval for this study has been granted by the research ethics committees of the four participating hospitals: St James' Hospital/Adelaide Meath Hospital Dublin, incorporating the National Children's Hospital research ethics committee, Beaumont hospital ethics medical research committee, St Vincent's Healthcare Group Ltd ethics and medical research committee and Mater Misericordiae University Hospital research ethics committee.

### Participants

Potential participants will be recruited from the physiotherapy waiting lists in the four participating hospitals if they meet the inclusion criteria as shown in Table 1.

**Table 1 T1:** Inclusion/Exclusion Criteria

**Inclusion Criteria**
1. Subjective complaint of hip pain with either hip internal rotation < 15° and hip flexion <115° or
2. ≥15° hip internal rotation and pain on hip internal rotation, morning stiffness less than or equal to 60 minutes, age > 50 years. (*American College Rheumatology Clinical criteria for the diagnosis of hip osteoarthritis*) [53]
3. Age 40–80 years except in 2 above (age >50 years).
4. Radiological evidence of osteoarthritis (2 of the following 3 criteria): osteophytes, joint space narrowing, ESR<20 mm/hr. (*American College of Rheumatology Criteria for the Classification and Reporting of Osteoarthritis of the Hip*) [53].
**Exclusion Criteria**
1. Previous hip arthroplasty, history of congenital/adolescent hip disease
2. Clinical signs of lumbar spine disease
3. Physiotherapy in previous 6 months
4. Pregnancy
5. Hip fracture
6. Contraindications to exercise therapy (unstable angina/blood pressure, myocardial infarction in previous three months, cardiomyopathy, uncontrolled metabolic disease, recent ECG changes, advanced COPD, third degree heart block)[54]
7. On waiting list for joint replacement within the next 27 weeks
8. Rheumatic diseases e.g. Rheumatoid Arthritis, Ankylosing Spondylitis, etc.
9. Intra-articular hip corticosteroid injection in previous 30 days
10. Insufficient English language to complete questionnaires

### Recruitment Procedure

All patients with a diagnosis of hip OA referred for physiotherapy from rheumatologists, GPs, orthopaedic consultants and other hospital consultants will be considered for inclusion in the RCT. Four physiotherapy departments in large acute hospitals in the Dublin area will be used: Beaumont Hospital, St Vincent's University Hospital, Adelaide Meath Hospital Dublin, incorporating the National Children's Hospital and Mater Misericordiae University Hospital.

Patients will be initially contacted by letter to explain the purpose of the study. A copy of the participant information leaflet will be enclosed. An initial telephone screening interview will be conducted to screen for major exclusion criteria and to provide the participant with more detailed information about the study. Potentially suitable participants will then be invited to attend an appointment with the blinded outcome assessor ([name]) who is a qualified physiotherapist. At this time, a comprehensive musculoskeletal examination will be undertaken to verify the volunteer's suitability for inclusion, based on the inclusion criteria outlined in Table 1. If eligibility is confirmed, patients will complete the consent form.

### Randomisation

Two computer generated randomisation lists have been drawn up by a statistician who is independent of the study. The first list will be used to randomize participants into one of the three arms of the trial. The second list will be used to re-randomise those subjects in the control group into one of the two intervention groups after the 9 week follow-up assessment. Both lists will be maintained by a member of the research team (TC) who will not be involved in the assessment or treatment of the participants.

Once informed consent has been obtained and baseline outcome measures have been completed, each participant will be randomly allocated to one of 3 groups

a. Exercise therapy

b. Exercise therapy and Manual Therapy

c. Control group (Waiting List)

Simple randomisation will be conducted. Group allocation will be communicated to the treating therapists in each treatment centre by the independent randomiser.

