### Sample Size Considerations

The primary outcome measure-WOMAC physical function subscale- has been used to estimate the sample size required. The minimum clinically important difference (MCID) has been ascertained [66]. Using an MCID of 5.4 (SD = 11) on WOMAC Likert scale, with a significance level of 0.05 (2 tailed) and a power of 80%, it is estimated that 67 patients are required per group. To allow for 10% attrition at the 9 week follow-up, it is estimated that 74 patients will be required per group. However, as the waiting list control group will be re-randomised into 2 treatment groups after the 9 week follow-up, 50 patients per group will be required to give a total sample size of 150 patients.

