### Statistical Analyses

These will be blinded and will be performed in consultation with a statistician. Baseline and demographic data will be presented using descriptive statistics. Differences from baseline will be calculated for all primary and secondary outcomes. Mean differences, standard deviations and 95% confidence intervals will be calculated for all continuous outcomes. A longitudinal repeated measures design will be used to assess change from baseline and to make between group comparisons for the continuous outcome measures. Comparisons will be made between the 3 groups at the 9 week period. Participants in the control group will be analysed according to the intervention received after the 9 week follow-up and comparisons will be made between the 2 intervention groups at 18 weeks (both with and without the re-randomised control group subjects at the 18 week period). This will be done on an 'intention to treat' basis. Participants will be analysed in the intervention groups to which they were originally assigned and will include withdrawels and patients not treated by the assigned intervention. Missing data will be replaced using the last observation carried forward. Per-protocol analyses will also be performed by excluding patients with deviations from the treatment protocol.

At the 9 week and 18 week time points, continuous variables will be analysed using a mixed ANOVA model (with treatment as the between group factor and time as the repeated factor), or the non-parametric equivalent if non-normal distributions apply. Where significant differences occur, post-hoc comparisons will be conducted using Tukey's multiple comparison procedure. Differences in nominal/ordinal data will be analysed using the χ^2 ^test. A significance level of 0.05 will be set for any inferential statistics conducted.

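### The pooled 18-week comparison of the two treatments merges two separate randomisations without a list term: no bias, but a chance imbalance is left unadjusted and a little precision is lost

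*Protocol article*

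**What the plan says.** Under Randomisation, the protocol article describes two computer-generated lists. The first allocates to exercise, exercise plus manual therapy, or waiting list. The second is for the waiting-list patients after their 9-week assessment: "The second list will be used to re-randomise those subjects in the control group into one of the two intervention groups". Randomisation is simple, with no blocking or stratification, and the allocation ratio of the second list is not given.

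Under Sample Size Considerations, the calculation arrives at 74 per group: "To allow for 10% attrition at the 9 week follow-up, it is estimated that 74 patients will be required per group". Because the controls are later re-randomised to the two treatments, the plan then accepts a smaller number: "50 patients per group will be required to give a total sample size of 150 patients".

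Under Statistical Analyses, the two treatments are compared at 18 weeks "both with and without the re-randomised control group subjects at the 18 week period". Continuous outcomes go into a mixed ANOVA with treatment between groups and time as the repeated factor. No factor for list, cohort or period is named.

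Under Outcome Measures, week 18 is the end of treatment for the former controls. For the original treatment arms, the end-of-treatment visit was at week 9.

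**The concern.** The pooled comparison is the one that brings each arm up to the required number, and it is built from two randomisations. For any control patient the second allocation comes nine weeks after the first. Good practice is to analyse by the groups within which patients were randomised, so list is a natural stratum.

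The article itself gives reasons to expect the cohorts' mean outcomes to differ at week 18. One cohort is just finishing treatment and the other finished about nine weeks earlier. The Background says that "the benefits of exercise for improving pain and function in hip OA appear to be short-term only". The Discussion plans to look at the effect of the waiting period on outcomes. If the means differ and the second-list share is unequal between the arms by chance, part of the cohort difference enters the treatment estimate, and the rest enlarges the residual. At stake is some precision, and some chance shift, in the comparison that justifies the total of 150.

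**Working it through.** **1. The plan's own figure.** Inputs from Sample Size Considerations: "Using an MCID of 5.4 (SD = 11) on WOMAC Likert scale", two-sided 0.05, 80% power.
- n per group = 2 × 11² × (1.960 + 0.842)² / 5.4² = 65.1, rounded up to 66. The t-test version gives 66.1, rounded up to 67. The plan's "it is estimated that 67 patients are required per group" is reproduced.
- 67 / 0.9 = 74.4 and 66 / 0.9 = 73.3, consistent with the stated 74.
- Pooled arms: 50 + 25 = 75 each, if the second list is 1:1. Without the re-randomised controls there are 50 per arm (45 after 10% loss), and power at 5.4 points is 69% (64%). The planned power therefore depends on pooling.

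**2. Chance difference in cohort mix.** Assumptions: 1:1 on the second list, every control reaches the second allocation, and all 150 are analysed (the plan carries the last observation forward). One third of the pooled patients come from the second list, so p = 1/3.
- SD of the difference in second-list share ≈ √[p(1 − p) × 2/75] = √(0.222 × 0.0267) = 0.077. Simulating the simple randomisation gives the same SD and a 95% limit of 0.15.
- If only 135 are analysed (150 less 10%), the simulated SD is 0.081 and the 95% limit is 0.16.

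**3. Shift in the treatment estimate.** Shift = D × difference in share, where D is the difference in mean outcome between cohorts at week 18. The documents do not give D. The range 2.7 to 5.4 points (half to one target difference) is an assumption.

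| D (points) | SD of shift | 95% limit | Limit as share of 5.4 |
|---|---|---|---|
| 0 | 0 | 0 | 0 |
| 2.7 | 2.7 × 0.077 = 0.21 | 0.41 | 8% |
| 5.4 | 5.4 × 0.077 = 0.42 | 0.82 | 15% |

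**4. Precision.** Without a list term the variance is 11² + p(1 − p)D², taking 11 as the within-cohort SD.
- D = 2.7: extra variance 0.222 × 7.29 = 1.62; share 1.62 / 122.62 = 1.3%.
- D = 5.4: extra variance 0.222 × 29.16 = 6.48; share 6.48 / 127.48 = 5.1%.
- Power for 5.4 points with 67 per arm is 81.1% with the term. Without it, power is 80.6% at D = 2.7 and 79.1% at D = 5.4. The n per arm for 80% power rises from 66 to 67 and 69.
- Simulated trials with 135 analysed and D = 5.4: power 78.3% without the term, 80.2% with it. At D = 0: 80.9% and 80.5%.

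**5. Validity.** In the same simulations the mean estimate equalled the true effect, and type I error was 4.8% to 5.1%, with or without the term.

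**6. What a treatment-by-list test could show.** SE of the interaction = 11 × √(2/n₁ + 2/n₂), where n₁ and n₂ are the numbers per arm from each list.
- 50 and 25 per arm: SE 3.8, power 29% for a 5.4-point interaction.
- About 40 and 22 per arm after losses: SE 4.1, power 26%.

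**The case against.** The strongest reply is that nothing here is invalid. With equal allocation on the second list, the mix is balanced on average, the estimate is unbiased, and the standard error already reflects the chance imbalance. The same could be said of any prognostic variable left out of a randomised comparison. That stands. A reader might infer from the pooling that the 18-week result is biased or that its p-value is wrong; the documents do not support this. The shift would become systematic only if the second list's ratio differed from that of the two treatment arms on the first list, and nothing in the article says so.

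A reader might also infer that the plan never checks whether the cohorts agree. That is too strong. It runs the comparison with and without the former controls, and the Discussion gives the effect of the waiting period as the reason. This is an indirect check, since it compares a subset with the whole that contains it. It does not adjust the pooled estimate or show the second-list effect separately.

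D is also not in the documents. The Background remark about short-term benefit gives neither a size nor a time frame, so a fade within nine weeks is inference. The reason to expect a non-zero D rests largely on the unequal time since treatment, which is a separate issue.

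Finally, the article is condensed, and covariates are often left to an analysis plan. Here, however, the article does name the model's factors, and list is not among them.

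**Conclusion.** The point holds as a small, nearly costless improvement, not as an error that threatens the result. The comparison that the sample size depends on pools two simple randomisations, and the stated model ignores which one a patient came from. The consequence is an unadjusted chance shift with SD about 0.21 to 0.42 points (95% limit 0.41 to 0.82) and a loss of about 1 to 5% of residual variance, or roughly 0.5 to 2 percentage points of power. Both vanish if the cohorts do not differ.

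These figures rest on a 1:1 second list, all 150 patients being analysed, a within-cohort SD of 11, and an assumed cohort difference of 2.7 to 5.4 points.

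**What to change.** In the pooled 18-week model, add randomisation list (first or second) as a fixed factor, and state the allocation ratio of the second list. Beside the planned analyses with and without the former controls, report the combined-versus-exercise difference within each list with its confidence interval. Present these descriptively, because an interaction test would have only about 26 to 29% power for 5.4 points, and a non-significant result should not be read as agreement.

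The cost is one degree of freedom and a row or two in a table. List membership is already known for every patient, and trial conduct does not change.

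The list term does not resolve the separate matter that week 18 is end of treatment for one cohort and about nine weeks later for the other. That concerns which effect is being estimated and needs its own decision.

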## Discussion

This paper outlines the protocol for a multicentre RCT that will compare the effect of a combination of manual therapy and exercise therapy, exercise therapy only and a waiting-list control on physical function in osteoarthritis of the hip. A multicentre approach was chosen to maximize the sample size and to improve generalisability of the results. This study is in keeping with Meinert's definition of multi-centre, where the data are acquired from two or more settings that are organizationally independent, a common intervention and data-collection protocol are used, and data management and analysis are centralized [94]. Although the setting of the four centres is similar, there may be differences in the demographic and socioeconomic profile between the sites, which are located in different geographical areas within an urban setting.

A number of methodological elements have been included in the trial to minimize bias such as power calculation, randomization, concealed allocation, blinded outcome assessment and intention-to-treat analysis. The reporting of the study will be in keeping with CONSORT guidelines [51], including recent recommendations for the reporting of non-pharmacological studies [52].

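### Simple randomisation over four hospitals, with only treatment and time in the stated model, is valid but accepts chance imbalance that hospital-stratified blocks and a hospital term would cheaply avoid

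*Protocol article*

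**What the plan says.** All places are in the protocol article.

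- **Randomisation:** two computer-generated lists exist, one per stage. "The first list will be used to randomize participants into one of the three arms of the trial"; the second reallocates the waiting-list controls to the two treatments after week 9. The method is given as "Simple randomisation will be conducted". Neither blocking nor stratification is mentioned.
- **Recruitment Procedure:** "Four physiotherapy departments in large acute hospitals in the Dublin area will be used".
- **Discussion:** the settings are described as similar, but "there may be differences in the demographic and socioeconomic profile between the sites".
- **Sample Size Considerations:** "50 patients per group will be required to give a total sample size of 150 patients". The controls are then to be divided between the two treatment groups.
- **Statistical Analyses:** changes from baseline are computed, and continuous outcomes go into a mixed ANOVA "with treatment as the between group factor and time as the repeated factor". No hospital term is named.

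**The concern.** The article names a possible source of variation between sites, and neither the allocation method nor the stated model deals with it. Therapists at each hospital deliver the treatments from a semi-structured exercise protocol and a choice of manual techniques, so delivery could also vary by site.

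With unrestricted allocation, nothing holds the arms near the planned 50 or keeps them balanced within a hospital. At stake are the precision of the treatment comparisons and how credible the comparison looks if one hospital's patients happen to fall mostly in one arm. The validity of the trial is not at stake.

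**Working it through.** **Inputs from the article.** N = 150, three arms, 50 per arm intended, four hospitals, difference 5.4, SD 11, two-sided 0.05, power 80%, 10% attrition at 9 weeks.

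**Inputs assumed.** Hospital sizes and the between-hospital SD are not given. Sizes are taken as equal (38/38/37/37), then varied. The between-hospital SD τ in change on WOMAC function is taken as 1 to 4 points.

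**1. The plan's own figure.** n = 2 × (1.960 + 0.842)² × 11² / 5.4² = 65.1, so 66 by the normal approximation. The t-based value is 66.1, rounded up to 67. The stated 67 per group is reproduced.

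**2. Arm sizes.** The SD of one arm is √(150 × 1/3 × 2/3) = 5.8. Multinomial simulation (200,000 draws) gives:

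| Event | Probability |
|---|---|
| Smallest arm 42 or fewer | 28% |
| Largest minus smallest arm 10 or more | 61% |
| Largest minus smallest arm 15 or more | about 31–32% |

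**3. Balance within hospitals.** With about 37.5 patients in a hospital, the difference between two given arms has variance 37.5 × 2/3 = 25, so SD 5. With a continuity correction, P(|difference| ≥ 6) ≈ P(|Z| ≥ 5.5/5) = 0.271. Over four hospitals, 1 − (1 − 0.271)⁴ = 0.72. Simulation also gives 72%. With sizes 50/41/34/25 it gives 71%, and with 60/45/30/15 it gives 70%, so the result barely depends on the size assumption.

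**4. Power cost of unequal arms.** Power = Φ(5.4/SE − 1.96), with SE = 11 × √(1/n₁ + 1/n₂).

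- Balanced, 45 v 45 after attrition: SE = 2.32 and power is 64.4%.
- Averaged over simple randomisation: 63.9%, a loss of about 0.5 points.
- 42 v 50 randomised, less 10%: about 60%.
- 18-week comparison with the controls pooled in, if the second list is also simple: 81.1% on average against 81.4% balanced.

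**5. Shift from hospital imbalance.** The chance shift in a pairwise difference has SD of about τ′ × √(1/50 + 1/50) = 0.2τ′, where τ′ is the SD of the hospital effects across patients. If τ is the usual SD of four equal-sized hospitals' effects (divisor 3), τ′ = τ√(3/4) and the shift is 0.17τ:

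- τ = 1: SD about 0.2 points.
- τ = 4: SD about 0.7 points, with 95% of shifts within about 1.4.

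If τ is read directly as τ′, the upper figure is 0.8. The comparison values are SE 2.32 and a target difference of 5.4.

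**6. Gain from a hospital term.** Replacing the SD of 11 by √(121 − τ′²) at 45 per arm raises power from 64.4% to 64.7% (τ′ = 1) or 70.5% (τ′ = 4).

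**7. After the fix.** Simulated hospital-stratified permuted blocks of 3, 6 or 9 (20,000 runs for each of the three size patterns) gave a largest-minus-smallest arm gap of at most 9, with 95th percentile at most 5. The gap within any hospital was at most 3. The required N does not change.

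**The case against.** **The method is sound.** Simple randomisation is unbiased, and its standard error and type I error already allow for chance imbalance. This stands: the article contains no error or contradiction here, only a less efficient choice.

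**A reader might infer that arm is confounded with hospital.** The documents do not support that. Patients are randomised individually, so every arm is expected at every hospital. Because changes from baseline are analysed, stable differences in level between hospitals largely cancel, and only differences in change matter. The article also calls the settings similar and trains all therapists to a common approach.

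**A reader might blame this for low power at 9 weeks.** The 64% follows from using 50 per group instead of the 74 that the article's own calculation asks for. That is a separate issue, and simple randomisation adds about half a point to it.

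**A reader might infer that both lists are simple.** The statement follows the three-arm allocation, and the article does not say outright that it covers the second list.

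**An unseen analysis plan may add hospital to the model.** That is possible, so the absence of the term is not a fault by itself. A later analysis plan could recover precision but could not change how patients were allocated.

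**Blocking has a cost.** Therapists are unblinded and learn allocations at their own site, so blocks within a hospital add some predictability. This stands, but varying block sizes and a list held outside assessment and treatment limit it.

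**Conclusion.** The point holds as a cheap improvement. The article fixes an allocation method that leaves avoidable imbalance: arm SD 5.8, a 28% chance of an arm of 42 or fewer, and a 72% chance of a gap of 6 or more between two given arms in at least one hospital. The expected harm is a modest loss of balance and precision: about 0.5 power points from unequal arms, and a chance shift of SD about 0.2 to 0.7 WOMAC points.

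The arm-size figures need only N = 150 and equal allocation, and the power figures add the plan's own difference, SD and attrition. The hospital gap assumes equal recruitment but changes little without it. The size of the shift depends entirely on the assumed between-hospital SD of 1 to 4 points, for which the article gives no basis.

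**What to change.** - Have the independent statistician generate both lists as permuted blocks of randomly varying, concealed size, stratified by hospital. This nearly removes the imbalance; incomplete last blocks leave a few patients' difference.
- Include hospital as a factor in the primary model. In the 18-week analyses that pool in the re-randomised controls, also include a factor for original versus re-randomised cohort.
- The article says the lists have already been drawn up. If the first is in use, leave it, stratify the second by hospital and add the hospital factor.

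The cost is two regenerated lists and one or two model terms. The sample size does not change and no new data are needed, since each patient's hospital is known. The downside is slight predictability within blocks at unblinded sites, limited by the varying block sizes and the central holding of the lists.
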